### Schedule and content of study follow up visits and telephone encounters

#### Study Visit 1 at day zero: Non-pregnant, HIV negative women with positive treponemal test and RPR titer ≥1:16 and meeting inclusion criteria will be offered enrolment

Informed consent will be completed by a study nurse prior to RPR testing, and baseline clinical information including symptom review, medical and sexual history, physical exam will be collected. Patients not consenting to participate in the study will receive treatment per national treatment guidelines for syphilis.

Subject data will be collected on study specific case report forms. Baseline treponemal result and RPR titer, signs and/or symptoms of syphilis and other STIs, will also be collected. Data will be entered into a central database using patient identification numbers only. Venipuncture will be performed, and blood will be collected for RPR quantitative titers Table 3.

**Table 3 Tab3:** Schedule of venipuncture specimen collection visits

Visit number	Scheduled visit	Allowed specimen collection interval outside of scheduled visit date
1	Screening	RPR test, HIV (eligibility checking)
2	Enrolment	Not applicable
3	3 months	10 days before or 45 days after
4	6 months	44 days before or 45 days after
5	9 months	44 days before or 45 days after

Once specimens have been collected and RPR results return at values equal to or greater than 1:16, subjects will be randomly assigned to one of two groups:
Group A: standard of care or penicillin groupGroup B: experimental group or cefixime group

Participants of Group A will receive treatment for syphilis with BPG according to national STI treatment guidelines. Participants in group A will be instructed to remain in the clinic for observation for 30 minutes after receiving this penicillin injection. According to national syphilis treatment guidelines, patients receiving penicillin may be asked to return for additional injections. These study participants will be asked to visit the clinic 3, 6 and 9 months after the day they received BPG for evaluation and RPR testing. BPG will be provided by the Brazil Ministry of Health.

Participants of Group B will receive their first dose of 400 mg cefixime at the study clinic under direct observation. Patients receiving cefixime will be instructed to remain in the clinic for observation for 30 minutes after receiving the medication. Participants will be given the cefixime pills and instructed on how and when to take their medication at home which they must continue for 10 days. Daily phone calls and text messages will be made to the patients by a study nurse to ascertain adherence to study medication and record side effects. Patients will be asked to bring back any unused study medication to their next visit two weeks following enrolment. Study participants receiving cefixime will also be asked to return to the clinic for scheduled visits 3, 6 and 9 months after the day of the last dose of cefixime for evaluation and RPR testing.

#### Study Visit 2 at two weeks following enrolment (allowable two days before or five days after scheduled visit):

Participants receiving cefixime will return to the clinic two weeks after enrollment for assessment of treatment compliance, evaluation resolution of symptoms if present at enrollment, and to ascertain any toxicities. Subjects will be asked to return for a scheduled clinical and laboratory assessment (Study Visit 3) at three months following enrollment.

### Phone call at 30 days following enrolment

A phone call to study participants randomized to cefixime will be conducted to perform a final evaluation of safety (side effects and adverse events) following the completion of the course of study drug.

#### Study Visit 3 at three months following enrolment (allowable 10 days before or 45 days after scheduled visit):

At Study Visit 3, subjects that received either cefixime or BPG will be asked questions regarding their current symptoms, interval sexual history, concomitant antibiotic use and possible adverse reactions. Subjects will have a venipuncture blood specimen collected for syphilis testing (RPR). For clinical safety, those subjects who experience a fourfold (two titer) increase in RPR titer at three months post treatment will be considered a treatment failure and will receive benzathine penicillin treatment according to national guidelines. All participants will undergo pregnancy testing. Those that are found positive on pregnancy testing will be treated for syphilis according to national guidelines and removed from the study. Subjects that received either cefixime or BPG will be asked to return at six months from the time of treatment.

#### Study Visit 4 at six months following enrolment (allowable 44 days before or 45 days after scheduled visit):

Subjects that received either cefixime or BPG will be asked questions regarding their current symptoms, interval sexual history, concomitant antibiotic use and possible adverse reactions if they received cefixime. Subjects will have a venipuncture blood specimen collected for syphilis testing (RPR) increase in RPR titer at 3 or 6 months post treatment. Those subjects who experience a fourfold (two titer) increase in RPR titer at three or six months post treatment will be considered a treatment failure and will receive BPG 2.4 million units IM once per week three weeks. Data for these patients through Study Visit 4 will be included in analyses, and for analysis purposes, these patients will be considered to be treatment failures. All participants will undergo pregnancy testing. Those that are found positive on pregnancy testing will be treated for syphilis according to national guidelines and removed from the study. A voluntary repeat HIV test will be performed at 6 months. Patients that test positive for HIV at 6 months will be referred for HIV care. No additional treatment for syphilis will be provided based on HIV-positive status other than according to the study protocol. Response to treatment of these patients will be included in the analysis. Subjects that received either cefixime or BPG will be asked to return at 9 months from the time of treatment.

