### Outcome measures

#### Primary outcome measure

The primary study outcome will be based on the change in the RPR titer from baseline to six months. Those subjects who have a 4-fold decrease in RPR titers from baseline by six months will be considered a positive treatment response (treatment success). All other participant outcomes will be defined as treatment failure including those subjects who experienced a fourfold (two titer) increase in RPR titer at three or six months post treatment and received BPG 2.4 million units IM once per week for 3 weeks.

**Note:** Subjects that received either cefixime or BPG that experience a 4-fold titer decline by three or months followed by a 4-fold titer rise by six or nine months will be classified as (1) treatment success at three months and (2) syphilis re-infection during the period following the initial 4-fold RPR titer decline.

**Note:** While there are limited data on the use of cefixime for the treatment of syphilis, cefixime is a broad spectrum, third generation cephalosporin in the same class and family as ceftriaxone for which extensive data on treatment efficacy for syphilis are available. RPR titers will be monitored frequently in this study and treatment with BPG will be provided if RPR titer increases fourfold (2 titer) at 3 or 6 months or does not reflect an adequate response (fourfold or 2-titer decline) at 6 months.

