### Study outcomes evaluation

#### Primary analysis

The primary outcome is the proportion cured using cefixime treatment, evaluated at six months post-recruitment.

Proportion representing proportion cured using cefixime treatment success, cure defined as at least 4-fold reduction in RPR titer by six months (compared to baseline). Participants experience a 4-fold reduction in RPR before six months will be counted as a success at six months.

The primary analysis will assess whether the proportion cured is greater than or equal to 90% and whether the observed efficacy is statistically different than the minimally acceptable efficacy set at 80%. Proportion cured and 95% confidence intervals will be calculated using the binomial exact test. Cefixime will be declared efficacious if the lower limit for a two-sided 95% confidence interval (CI)≥ 0.80.
*Cure:* At least a 4-fold decrease in RPR from baseline to 6 months.*Failure:* Less than a 4-fold decrease in RPR titer from baseline to 6 months, or an increase in RPR titer.*Non-evaluable:* At least one of the following: Subject did not return for 6 month visit, or RPR results from the 6 month visit were not available for any reason, or subject could not be evaluated for any other reason.

For the PP analysis population, subjects with non-evaluable outcome status will be excluded from the analysis. For the ITT analysis population, subjects with non-evaluable outcome status will be included in analyses and classified as treatment failures. Subjects who discontinued early from the study due to a lack of treatment effect are included in all analysis populations as treatment failures.

The primary efficacy analysis will be based on the cure rate by 6 months and will be performed in the PP analysis population. The primary analysis will also be performed in the ITT population, but this is a secondary outcome measure.

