### Ethical concerns

#### Potential risks

Potential risks to study participants include the possibility that the alternative treatment may not prove to be effective. For this reason, we will closely follow the subjects for adherence to study medication including daily phone or in-person contact to establish adherence to study drug. RPR titers will be collected 12 weeks after completion of treatment (with no more than 5-day result turnaround time). If the participant experiences an RPR titer increase of 4- fold or more from the entry RPR at 3 or 6 months, we will consider this a treatment failure and the participant and be given 2.4 million units of BPG immediately and according to national guidelines.Risks to privacy: Participants’ attendance at study visits may be accidentally noticed by others.Psychological risks: Receiving a positive syphilis diagnosis could be upsetting to a participant. However, syphilis diagnosis occurs as part of standard clinical care and outside of the study.*Risks associated with blood draw*: Participants may experience discomfort, bruising, or even fainting in connection with the blood draw that will be performed during the visits. There is also a slight risk of infection.Cefixime is contraindicated in patients with known allergy to cefixime or other cephalosporins. Some participants may not be aware of their allergy status. However, anaphylactic or anaphylactoid reactions (including shock and fatalities) have rarely been reported with the use of cefixime, thus this risk is considered to be very low.Some adverse reactions were documented in other cefixime clinical trials. In United States (U.S.) trials of the tablet formulation of cefixime, the most commonly seen adverse reactions were gastrointestinal events. These events were reported among 30% of adult patients that received either the twice daily or the once daily regimen. Discontinuation of cefixime during the U.S. clinical trials occurred among 5% of study participants because of drug-related adverse reactions. Other individual adverse reactions reported from U.S. clinical trials included diarrhea (16%), nausea (7%), loose or frequent stools (6%), flatulence (4%), abdominal pain (3%), and dyspepsia (3%). Observed and reported adverse reactions for cephalosporins including but not limited to cefixime have included allergic reactions, superinfection, renal dysfunction, toxic nephropathy, hepatic dysfunction including cholestasis, aplastic anemia, hemolytic anemia, hemorrhage, and colitis.In this study, participants will be observed for 30 minutes in the clinic following the first dose of cefixime. In the event of an adverse event or an allergic reaction possibly related to cefixime, participants will be evaluated by a study nurse and by a clinic-based study physician. Participants will be referred to emergency services at the discretion of the clinic-based study physician. Cefixime will be discontinued in the event of an allergic reaction.The efficacy of cefixime to prevent mother-to-child transmission of syphilis is unknown. Study participants will be counseled regarding the risk of untreated syphilis in pregnancy. Each participant will be offered oral contraceptive tablets as well as condoms to prevent pregnancy for the duration of the study. Condoms will be provided to each participant and use will be encouraged at each visit to reduce the risk of re-infection with syphilis and infection with other STIs.

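### Rescue penicillin for non-response at 6 months is promised under the outcome measures but is missing from the Visit 4 procedure and the risk section

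*Protocol article*

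**What the plan says.** The rule for giving rescue BPG appears in several places in the protocol article.

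- **Primary outcome measure, second note.** BPG is promised after a fourfold rise at 3 or 6 months, and also when the titer "does not reflect an adequate response (fourfold or 2-titer decline) at 6 months".
- **Study Visit 4.** "Those subjects who experience a fourfold (two titer) increase in RPR titer at three or six months post treatment will be considered a treatment failure", followed by the BPG course. No other RPR result at this visit leads to treatment. Women from both arms are then asked back at 9 months.
- **Potential risks.** The safeguard is again tied to a rise: "If the participant experiences an RPR titer increase of 4- fold or more from the entry RPR at 3 or 6 months".
- **Study Visit 3.** A fourfold rise at 3 months leads to BPG. This agrees with every other section.
- **Study Visit 5.** RPR is drawn, but no action on the result is stated.

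The analysis definition of failure is wider than the rise. Under Primary outcome measure, anyone without a fourfold decrease by 6 months fails: "All other participant outcomes will be defined as treatment failure". Under Primary analysis, failure is "Less than a 4-fold decrease in RPR titer from baseline to 6 months, or an increase in RPR titer". A fourfold fall at an earlier visit is kept as a success: "Participants experience a 4-fold reduction in RPR before six months will be counted as a success at six months". The section on study population and follow-up status also promises a description of the women who received rescue BPG.

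**The concern.** The women at issue are those whose titer neither falls nor rises fourfold by 6 months. The trial calls them failures, and the outcome note says they will be treated. The step-by-step instruction for the visit at which their failure becomes known does not say so, and neither does the section that describes how participants are protected if cefixime does not work.

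Staff working from the visit text alone would find no direction to treat such a woman, and the 9-month visit gives none either. She could leave the trial with a recorded treatment failure and no further penicillin. If some sites followed the outcome note and others the visit text, the table of rescue recipients would also mix two rules, and the 9-month titers of non-responders would be read after different care.

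**Working it through.** The plan states no figure on this point, so the check is a comparison of text with a small titer calculation.

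**Step 1. Triggers side by side.**

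| Section | Fourfold rise | No fourfold decline at 6 months |
|---|---|---|
| Study Visit 3 | BPG (at 3 months) | not applicable |
| Study Visit 4 | BPG (at 3 or 6 months) | not stated |
| Study Visit 5 | no action stated | no action stated |
| Primary outcome measure, second note | BPG (at 3 or 6 months) | BPG |
| Potential risks | BPG (at 3 or 6 months) | not stated |

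**Step 2. Which titers fall between the two rules.** Let T be the reciprocal entry titer. Cure needs T/4 or lower. The rise trigger, counted from entry as in Potential risks, needs 4 × T or higher. At the eligibility minimum of 1:16:

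- cure: 16/4 = 4, so 1:4 or lower;
- rise trigger: 16 × 4 = 64, so 1:64 or higher;
- between them: 1:8, 1:16 and 1:32.

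For any entry titer, the same three two-fold steps lie in the gap: T/2, T and 2T.

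**Step 3. Does the reference point for the rise matter?** Visit 4 does not say what the rise is measured from. Suppose it were the 3-month titer. With entry 1:16, a woman with neither a fourfold fall nor a fourfold rise at 3 months was then at 1:8, 1:16 or 1:32. With three possible 6-month results in the gap, there are 3 × 3 = 9 sequences. Only 1:8 followed by 1:32 is a fourfold rise from 3 months (32/8 = 4). The other eight still meet no trigger, so the gap does not depend on the reference point. These are counts of possible sequences, not probabilities.

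**Step 4. Status of a woman in the gap.** Provided that she had no earlier fourfold fall:

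- analysis: failure, under both Primary outcome measure and Primary analysis;
- outcome note: BPG is owed;
- Visit 4 and Potential risks: no trigger met;
- Visit 5: no stated action.

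**Step 5. How many women?** Only a ceiling can be given. Taking the sample-size section's 20% dropout, the cefixime arm has 140 × 0.80 = 112 evaluable women. At its anticipated cure rate of 90%, failures number 112 × 0.10 = 11.2. At its minimum acceptable 80%, they number 112 × 0.20 = 22.4. Some of these failures will have risen fourfold and are covered everywhere. The document gives no such split, so the number relying on the outcome note alone lies anywhere from 0 to about 11, or from 0 to about 22. The BPG arm falls under the same rule, but no dropout assumption is stated for it.

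**The case against.** The strongest reply is that nothing is contradicted. The outcome note makes a plain commitment that covers these women. Visit 4 and Potential risks say what happens after a rise; neither says that BPG is given after a rise alone. A reader who follows every section together arrives at the two-part rule. This stands: the fault is incomplete repetition of a rule, and the two-part rule remains the protocol's commitment.

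Second, the Visit 4 paragraph is visibly damaged just before the trigger, so words may have been lost there. That weakens Visit 4 as evidence taken alone. It does not account for Potential risks, where the trigger is legible and has the same omission.

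Third, this is a journal article, and the full protocol and site procedures are not shown. They may carry the whole rule, so harm to any participant is conjecture. The mismatch is still on the page: the article states the 6-month trigger in three places, and the two incomplete statements are the visit procedure and the participant safeguard.

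Three stronger readings are tempting, and the document supports none of them.

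- *Non-responders go without rescue.* The outcome note promises them BPG.
- *The primary result is biased.* These women are failures at 6 months whether or not they are re-treated.
- *The rescue doses conflict.* A reader might set "received BPG 2.4 million units IM once per week for 3 weeks" against "be given 2.4 million units of BPG immediately and according to national guidelines" and see three doses against one. The second wording can equally mean a first dose at once and the rest as the guideline directs; the enrolment-visit text says that patients on penicillin may be called back for further injections under it. Whether the wordings differ in practice depends on the national guideline, which is not shown. No dose conflict is claimed, and no particular regimen is recommended.

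**Conclusion.** The concern holds as a minor inconsistency that bears on participant safety. The two-part rescue rule is complete in one place and reduced to its first part in the two places that describe the 6-month action and the safeguard. The gap covers three 6-month results for any entry titer, in either arm, for women with no earlier fourfold fall. This takes the rise as measured from entry; measuring it from 3 months would close only one of the nine sequences.

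The 6-month primary analysis is unaffected. What could suffer is the care of an individual woman and the consistency of the rescue-therapy table. The number of women affected cannot be derived from the document, and the number actually left untreated may be zero. Confidence is high that the texts differ, and much lower that any site would act on the shorter one.

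**What to change.** In the Study Visit 4 text and in Potential risks, extend the BPG trigger with the clause *or less than a fourfold decline at 6 months*, so that both match the second note under Primary outcome measure. Repair the damaged sentence before the Visit 4 trigger in the same edit. Visit 5 needs no change once the 6-month rule is complete.

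The cost is one clause in each of two sections. No patients, visits, tests or changes to the analysis are needed, and the change only spells out treatment that the protocol already promises.

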#### Secondary outcome measure

The secondary outcome measure is the safety and tolerability of cefixime as a treatment for syphilis.

This will be measured by the percent of treated patients experiencing mild, moderate, severe, or life-threatening adverse events, either temporally associated or not associated with the study product. Patients will be instructed on the possible side effects of the study drug, and when to call the study team should they experience any of these side effects. We will use the Common Terminology Criteria for Adverse Events (CTCAE) [35] to evaluate side effects and the severity of grade (scale 1–4). Women reporting a toxicity of grade 3 or greater, that is or probably related to study drug (to be determined by a physician not associated with the study), during the treatment period will be asked to stop study treatment, return to the clinic, and they will be treated with 2.4 million units of BPG. Patients will be followed closely until the toxicity returns to a grade 2 or less.

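### Rescue penicillin after a fourfold RPR rise is a fixed three-week course in two sections and guideline-based in two others, and the protocol does not say which prevails

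*Protocol article*

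**What the plan says.** Four places in the protocol article state what happens to a woman whose RPR titre rises fourfold after treatment.

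- **Study Visit 3.** The trigger is a "fourfold (two titer) increase in RPR titer at three months post treatment". Such a woman "will be considered a treatment failure and will receive benzathine penicillin treatment according to national guidelines". No dose or number of injections is stated.
- **Study Visit 4.** The trigger is a "fourfold (two titer) increase in RPR titer at three or six months post treatment", so month 3 is expressly included. These women "will receive BPG 2.4 million units IM once per week three weeks".
- **Primary outcome measure.** Among the failures it lists women with such a rise at month 3 or 6 who "received BPG 2.4 million units IM once per week for 3 weeks".
- **Potential risks (under Ethical concerns).** For a rise of fourfold or more over the entry titre at month 3 or 6, the woman is to "be given 2.4 million units of BPG immediately and according to national guidelines".

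A note under Primary outcome measure adds that BPG will also be given when the titre has not fallen fourfold by 6 months. It names no regimen.

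The protocol says how it understands guideline BPG in two places. The Methods paragraph of the abstract ties it to the stage of infection. The Study Visit 1 section says that women treated under the national guideline may be asked back for more injections.

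**The concern.** Rescue penicillin is one of the protocol's protections for women given a drug whose effectiveness against syphilis it calls uncertain. The Study Visit 3 section presents the month-3 rule as a matter of clinical safety. A protection of that kind should be stated once, or stated identically each time.

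Here the instruction depends on the section that is read. A nurse working from the Visit 3 text would follow the guideline for the woman's stage. A nurse working from the Visit 4 text would book three weekly injections. Both would be following the protocol, and a monitor would have no basis for calling either a deviation. The planned table describing women who received rescue BPG (Efficacy and other analysis plan, Study population and follow-up status) could then cover more than one treatment under a single label.

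**Working it through.** There is no statistical figure to reproduce. The check sets the sections side by side.

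**Step 1: is it the same event?** At month 3 the only earlier titre is the one at entry, so a fourfold rise at that visit meets the trigger in all four sections. A rise over entry at month 6 meets the trigger in Study Visit 4, Primary outcome measure and Potential risks. The sections cannot be separated into one rule for month 3 and another for month 6, because the Visit 4 and primary outcome texts both name month 3. Even if they were separated, Study Visit 4 and Potential risks would still differ at month 6.

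**Step 2: what does each section prescribe?**

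| Section | Event | Instruction | Amount stated |
|---|---|---|---|
| Study Visit 3 | rise at month 3 | BPG per national guideline | none |
| Study Visit 4 | rise at month 3 or 6 | 2.4 million units weekly, three weeks | 3 × 2.4 = 7.2 million units |
| Primary outcome measure | rise at month 3 or 6 | same course as Visit 4 | 3 × 2.4 = 7.2 million units |
| Potential risks | rise at month 3 or 6 | 2.4 million units at once, and per guideline | 2.4 million units plus whatever the guideline adds |

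**Step 3: could the wordings mean the same thing?** Only if the guideline prescribes three weekly doses for every such failure. The guideline is not shown. Where the protocol describes guideline BPG, it makes it depend on stage and treats additional injections as a possibility. The Discontinuation of study enrolment section also refers to women whose original treatment was one penicillin injection. Within this document, therefore, guideline treatment is not always a three-injection course.

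**Step 4: does any section settle the matter?** No section gives one wording precedence, and none cross-refers to another.

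**Step 5: does the primary result change?** No. The Visit 4 section and the primary outcome definition count these women as failures, and the number of rescue injections plays no part in that. The separate note on a fall followed by a rise also classifies by titre alone.

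**The case against.** The strongest reply is that the difference may vanish in practice. The guideline is unseen, and the protocol's descriptions of guideline BPG concern initial treatment, not re-treatment after serological failure. If the guideline calls for three weekly doses in that situation, all four sections agree. This stands as a limit on how far apart the instructions are. It does not remove the fault, because nothing in the protocol tells staff that the wordings are equivalent.

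Several stronger readings are tempting, and the documents do not support them.

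- **Three distinct regimens.** A reader might count three. The Potential risks wording can be read as guideline treatment started at once. The firm conflict is between the fixed course (Study Visit 4, Primary outcome measure) and guideline-based treatment (Study Visit 3, Potential risks).
- **One to three injections for the same event.** No section states a single injection for serological failure.
- **A conflict over toxicity stops.** The Secondary outcome measure section says of these women that "they will be treated with 2.4 million units of BPG". That is the only regimen given for that event, so there is nothing for it to contradict.
- **A count of affected women from the assumed cure rates.** Non-cures at 80% to 90% cure include women whose titre merely failed to fall. The conflicting instructions apply to fourfold rises, for which no rate is given.
- **Failure defined by the rescue course.** The primary outcome text already classes every outcome other than success as failure and names the re-treated women as included. No redefinition is needed.
- **Differences by site.** The protocol has no site-specific rule. It leaves room for staff to differ, but does not show that sites would.

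**Conclusion.** The point holds as an internal contradiction in participant management. For a fourfold RPR rise at month 3, and again at month 6, the protocol prescribes a fixed three-week BPG course in two sections and guideline-based BPG elsewhere, with no rule of precedence.

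The consequence is confined to consistency of care and to how rescue treatment is reported. The cure rate, its confidence interval and the sample size are untouched. The number of women involved cannot be derived from the document. The practical gap between the instructions depends on a guideline that is not shown and could be narrower than the wording suggests.

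It should still be corrected, because it concerns the safety provision for women whose treatment has failed and the correction is cheap. No view is taken here on which regimen is right.

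**What to change.** Reconcile Study Visit 3, Study Visit 4, Primary outcome measure and Potential risks to a single rescue rule for a fourfold rise. Either state it once and have the other sections refer to it, or repeat it word for word. The clinical team decides its content. The note under Primary outcome measure on inadequate response at 6 months should refer to the same rule, since it now promises BPG without a regimen.

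The cost is a wording amendment and a memo to the sites. Sample size, data collection and the primary analysis do not change.
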